# 3. RATIONALE FOR PROPOSED STUDY

The absence of specific drug treatment and lack of vaccine is a critical gap in the knowledge of COVID-19 pandemic (38). And in this regard it is important to refer to a seminal paper published on the ‘responsibility and accountability of conducting standard research including randomized clinical drug trials by the medical community’ in times of epidemics, and the authors have used the recent Ebola virus epidemic in Africa to highlight their contention (39).

The Ministry of AYUSH, GOI has recommended the self-care guidelines for preventive health measures and boosting immunity with special reference to respiratory health based on Ayurvedic literature and scientific publications. However, this advisory does not claim to be treatment for COVID-19. The role of Ayurveda Rasayana as an immunomodulator is well known and should be investigated in COVID-19 (40). In this protocol, we describe the rationale for using three Ayurveda herbal formulations individually to treat COVID-19 as an add-on/adjunct therapy to standard of care. The three Ayurveda formulations are AYUSH-64, Sanshamani Vati Plus and Yashtimadhu. In India the guidelines issues by the Ministry of Health and Family Welfare are generally followed as standard of care (See above, Section 2.6 (20). It is difficult if not impossible to expect a uniform nature of standard of care in the study site hospitals in this study.

Patients suffering from symptomatic Mild to Moderate COVID-19 will be selected for this study. By ’Mild to Moderate’ it would essentially mean that patients do not require any of the emergency measures that are advocated for severe and life-threatening cases of COVID-19. The latter would include complications of progressive lung disease, septicemia, shock and other complications (see Table 3). The mild to moderate cases of COVID-19 will belong to the categories of ‘Mild’ and ‘Pneumonia’ as described by WHO (See WHO Table on Syndromes associated with COVID-19 shown in Section 2.6 above). Mere need for supplement oxygen using non-invasive means will not negate the classification of mild to moderate COVID-19.

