**Criteria of ‘Clinical Recovery’**:

1. Normal body temperature (≤36.6°C axilla or ≤37.2 °C oral)
2. Absence of cough or mild cough (infrequent, short episodic, non-wheezy, relieved by minimal or no medication, not interfering with routine speech and not related to lying in bed, mild sore throat or nasal congestion)
3. Absence of breathlessness on routine daily self-care chore or respiratory rate less than 30 breaths per minute without supplemental oxygen
4. Absence of any other symptom/sign attributed to COVID-19 illness
5. Normalization of SpO2 by standard peripheral oximetry device (above 95 percent)
6. Recovery should be sustained for at least 48 hours under physician observation
7. Assessed by physician blinded to treatment allocation
8. All of the above criteria ought to be fulfilled

Note: Clinical recovery would be deemed from the first day of satisfying the above criteria

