**11.2 Secondary Efficacy:**

1) Rate of patients with negative SARS-CoV-2 on nasal or throat swab in a 2-day continuous real time RT-PCR test beginning from ‘first day of clinical recovery’ (see above) or ‘Day 10 after onset of symptoms depending on whichever of the two time points is first achieved

2) Timelines (days counted from onset of illness) - normal body temperature <37◦C, absence or minimal cough (see ‘clinical recovery’ for the definition), absence of dyspnoea (respiration rate 24/minute or less on room air), onset of clinical pneumonia, pneumonia diagnosed on chest X-Ray or CT scan, time to supplemental oxygen, admit in intensive care unit, mechanical ventilation (non-invasive), mechanical ventilation (invasive), steroid use, respiratory failure, adult respiratory distress syndrome, cytokine storm syndrome, secondary infection, shock, septicaemia shock, hospital discharge, death, negative nose or throat swab confirmatory test, all-cause mortality (Time Frame: up to 28 days).

Note: In case of symptoms, the absence on improvement should be sustained for at least 72 hours or live hospital discharge, whichever comes first.

3) Proportion OF patients developing an event that reflects clinical or otherwise improvement of worsening (the events are similar to those listed under Timelines, see above)

4) Improvement on pulmonary function tests using simple ‘home expiratory spirometer’ device and peripheral pulse oximetry

5) Improvement in selected laboratory parameters: blood haemoglobin, differential and total leukocyte counts, liver enzymes, renal functions, acute phase reactants, serum IL-6 and other selected cytokines, serum muscle enzymes (CK, CPK), serum ferritin, serum d-Dimer, anti-oxidant markers, serum BNP (cardiac function)

6) Serological Protective Antibody Assay (IgM and IgG)

7) Radiological Improvement on digital chest Xray and HRCT chest

8) Drug related: side effects and toxicity, and tolerability

9) Health status: WHO QOL (Appendix M) brief, health related behaviour habit and fitness questionnaire based on visual analogue scale (See Appendix N)

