**CLINICAL STUDIES OF AYUSH 64**

1. The report on management of Chikungunya through Ayurveda and Siddha has documented the efficacy of ‘AYUSH-64’. (Anonymous. Management of Chikungunya through Ayurveda and Siddha, A Technical Report, CCRAS, Dept of AYUSH, MoHF&W, Govt of India, 2009)
2. Clinically effective in cases of Microfilariasis. (40)
3. 81% curative effect on Plasmodium vivax, drug is more effective in ring stage than in Gamete stage. In the cases of mixed infection of P. vivax & P. falciparrum the curative effect was found to be 75% after longer therapy. (41)
4. Clinically shown good effect in the management of microfilaraemia (42, 43)
5. In a study with about 4500 participants, Ayush-64 was found safe and nontoxic with good antimalarial activity and also observed that by giving Ayush-64 to all fevers along with anti- mosquito measures, there was a decline in the infectivity rate. (44)
6. A double-blind study demonstrated comparative efficacy of AYUSH 64 to the chloroquine /primaquine as the standard modern control in sixty cases of P. Vivax malaria. (45)
7. In a prospective, open-label, nonrandomized, single group, single-centre pilot study with pre-test and post-test design one-week intervention of ‘AYUSH 64’ in a dose of 3gms/day effectively helped to recover from Influenza Like Illness  symptoms and return to normal life early with reduced frequency of usage of acetaminophen/ antihistaminic. No adverse effects were found during the study (46).
8. A pilot study done on 112 participants produced 97.14% result with prophylactic treatment in P.F. Malaria (47)

**Note: The drug /drug and drug herb interactions may not be so relevant as the formulation is not NCE /and possess herbs processed as per Standard procedures of Ayurveda, however such studies may be taken up simultaneously**

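### The clinical recovery criteria do not say under what treatment temperature and SpO2 are read, and item 3 leaves the oxygen condition open to two readings

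*Combined protocol and SAP*

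**What the plan says.** Section 11.1 and Synopsis j give the same list of criteria for clinical recovery, and both primary outcomes (mean time to recovery and proportion recovered) use it.

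- Item 1: "Normal body temperature (≤36.6°C axilla or ≤37.2 °C oral". Antipyretics are not mentioned.
- Item 3: "Absence of breathlessness on routine daily self-care chore or respiratory rate less than 30 breaths per minute without supplemental oxygen".
- Item 5: "Normalization of SpO2 by standard peripheral oximetry device (above 95 percent". The oxygen being breathed is not mentioned.
- Item 6: "Recovery should be sustained for at least 48 hours under physician observation". This asks for durability, not for durability off treatment.
- Item 7 requires a blinded assessor, and item 8 says "All of the above criteria ought to be fulfilled". A note dates recovery from the first day on which the criteria are met.

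Only item 2 (cough) says anything about medication.

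Elsewhere, Section 11.2 item 2 ties a secondary timeline to room air: "absence of dyspnoea (respiration rate 24/minute or less on room air". Section 3 states "Mere need for supplement oxygen using non-invasive means will not negate the classification of mild to moderate COVID-19". Section 5 leaves standard of care to the treating physician, accepts variation between sites and patients, and has it recorded in the case record form. The daily progress report (Appendix J) has an oxygen row and a steroid row but no antipyretic row.

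**The concern.** Temperature and SpO2 are both readings that supportive treatment moves directly. A criterion that sets only a cut-off cannot tell a patient who has recovered from one whose reading is being held in range. The plan recognises this for cough in item 2 and for dyspnoea in Section 11.2, but not for the two numeric criteria of the primary definition.

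Two things are at stake. First, two sites could date recovery differently for the same patient on oxygen, depending on how they read item 3. Second, treatment allocation is open and supportive care is not standardised, so antipyretic or oxygen use could differ by arm. The blinded assessor in item 7 protects the reading itself, but not the treatment given before it. If controls received more such treatment, their recovery would be dated too early and a real effect would shrink. If the drug arm received more, the bias would run the other way.

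**Working it through.** **Step 1: apply the criteria as written to two patients.**

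| Patient | Item 1 | Item 3 | Item 5 | Counts as recovered, other items met? |
|---|---|---|---|---|
| Not breathless, SpO2 97% on nasal oxygen; oxygen condition covers all of item 3 | met | not met | met | No, by item 8 |
| Same patient; oxygen condition covers only the respiratory-rate alternative | met | met by first alternative | met | Yes |
| Axillary 36.5°C on an antipyretic, kept so for 48 hours | met | met | met | Yes, on either reading |

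The oxygen result turns on the scope of one phrase. The antipyretic result does not, because no item mentions antipyretics.

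**Step 2: who could be affected.** Inclusion criterion 1 requires a febrile illness, and Section 2.6 describes management as symptomatic and supportive, so antipyretic use is foreseeable. No rate is given. For oxygen, Section 3 keeps patients on non-invasive oxygen within mild to moderate disease. Against that, Section 9 lets the investigator withdraw a patient for persistent oxygen need, the exclusion criteria in Section 10 name oxygen support for more than one hour in their severity guidance, and Section 14 applies a stop rule to patients who become severe by those criteria. To count under item 6, recovery on oxygen would have to last 48 hours, so the group is probably small, though not empty.

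**Step 3: scale.** There is no plan figure to reproduce. Section 17.1 gives 70 per arm (70 + 70 = 140) without a power calculation. All rates below are assumptions, used with 70 per arm and two-sided 0.05 (Section 17.2).

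Let p be true recovery at a given time and m the share of patients not truly recovered who are counted as recovered. The observed rate is q = p + (1 − p)m. The chance of rejection is Φ((|q1 − q2| − 1.96·SE0)/SE1) plus the negligible other tail, with SE0 = √(2q̄(1 − q̄)/70) and SE1 = √((q1(1 − q1) + q2(1 − q2))/70).

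*Equal masking, true recovery 60% vs 80%.* At m = 0.2, q1 = 0.60 + 0.40 × 0.2 = 0.68 and q2 = 0.80 + 0.20 × 0.2 = 0.84. The difference falls from 20 to 16 points and power from 73.8% to 60.3%. At m = 0.1 power is 67.3%; at m = 0.3 it is 53.0%.

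*Unequal masking (m = 0.1 vs 0.3), no true effect.*

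| True recovery | Observed rates | Spurious difference | Rejections (nominal 5%) |
|---|---|---|---|
| 50% | 55% vs 65% | 10 points | 22.5% |
| 70% | 73% vs 79% | 6 points | 13.1% |
| 80% | 82% vs 86% | 4 points | 9.9% |

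With m = 0.1 vs 0.2 at 50% true recovery, the difference is 5 points and rejections are 9.2%.

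*Time to recovery.* Among patients in whom temperature is the last criterion met, shift = (gap in antipyretic use) × (days by which use advances the criterion). A gap of 25 points and 2 days gives 0.25 × 2 = 0.5 day. Gaps of 10 to 40 points and advances of 1 to 3 days give 0.10 × 1 = 0.1 to 0.40 × 3 = 1.2 days. The trial-level shift is this times the share of such patients. At an assumed share of 25% it is 0.5 × 0.25 = 0.125 day, with a range of 0.025 to 0.3 day. For comparison, Section 8 expects most discharges at 5 to 15 days.

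**The case against.** The other side has several sound points.

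- **Oxygen.** Item 3 already contains the oxygen condition and item 8 requires every item. On the natural clinical reading, a patient on oxygen is not recovered. A reader might infer from item 5 alone that such patients are plainly counted. The documents do not support that: they allow it on one of two readings, and Sections 9, 10 and 14 limit how many such patients remain. What stands is the ambiguity.
- **Difference between arms.** Appendix D reports an AYUSH 64 pilot with "return to normal life early with reduced frequency of usage of acetaminophen/ antihistaminic". A reader might infer that masking will be heavier in controls. The pilot was a single-group, nonrandomized, pre-test/post-test study in influenza-like illness at 3 g/day. It concerns one of the three drugs and has no control arm, so it cannot show a difference between arms. Such use could differ; the documents do not show that it would.
- **Safeguards.** Absence of other symptoms or signs, 48 hours under observation and blinded assessment all narrow the problem. None of them refers to the treatment under which a reading is taken.
- **Treatment policy.** Comparing drug plus standard of care with standard of care, whatever supportive care is given, is a legitimate question in an exploratory trial. An antipyretic-free condition inside the primary definition would also tie the outcome to unblinded prescribing. An arm given more antipyretic for myalgia, say, would recover later by definition. A fixed washout such as 24 hours has no basis in the documents. This stands, and it is why the antipyretic part belongs in recording and a sensitivity analysis.

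**Conclusion.** The point holds as a gap in the wording of the primary definition. Items 1 and 5 do not state the treatment conditions of the reading, and item 3 can be read so that a comfortable patient on oxygen qualifies. A temperature normalised by an antipyretic can count.

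The size and direction of any bias are unknown. The figures above rest wholly on assumed rates and show only that unequal masking could matter at 70 per arm. A reader might take 0.1 to 1.2 days as the shift in the trial's mean. It is not: it applies only where temperature is the last criterion met, and the documents do not give that share. The oxygen part is probably small in numbers but costs almost nothing to close. The wording and the recording should be settled before enrolment, because antipyretic timing that is not captured daily is hard to reconstruct from the general medication record.

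**What to change.** In both Synopsis j and Section 11.1:

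1. Reword item 5 to require a value above 95 percent on room air.
2. Reword item 3 so that the absence of supplemental oxygen applies to both alternatives, in line with the room-air condition in Section 11.2 item 2.
3. Keep item 8 and the dating note unchanged, so that recovery is dated from the first day on which all criteria hold.

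Then add an antipyretic row to the daily progress report in Appendix J (oxygen already has one). Prespecify in Section 17.2 a sensitivity analysis of both primary outcomes in which temperature counts as normal only on antipyretic-free readings, with the interval chosen and stated by the sponsor in advance.

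No prescribing changes; only the scoring of the outcome does. The cost is the rewording of two items in two places, one extra daily form field and one extra analysis. The downside is that a few recoveries will be dated later.

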**11.2 Secondary Efficacy:**

1) Rate of patients with negative SARS-CoV-2 on nasal or throat swab in a 2-day continuous real time RT-PCR test beginning from ‘first day of clinical recovery’ (see above) or ‘Day 10 after onset of symptoms depending on whichever of the two time points is first achieved

2) Timelines (days counted from onset of illness) - normal body temperature <37◦C, absence or minimal cough (see ‘clinical recovery’ for the definition), absence of dyspnoea (respiration rate 24/minute or less on room air), onset of clinical pneumonia, pneumonia diagnosed on chest X-Ray or CT scan, time to supplemental oxygen, admit in intensive care unit, mechanical ventilation (non-invasive), mechanical ventilation (invasive), steroid use, respiratory failure, adult respiratory distress syndrome, cytokine storm syndrome, secondary infection, shock, septicaemia shock, hospital discharge, death, negative nose or throat swab confirmatory test, all-cause mortality (Time Frame: up to 28 days).

Note: In case of symptoms, the absence on improvement should be sustained for at least 72 hours or live hospital discharge, whichever comes first.

3) Proportion OF patients developing an event that reflects clinical or otherwise improvement of worsening (the events are similar to those listed under Timelines, see above)

4) Improvement on pulmonary function tests using simple ‘home expiratory spirometer’ device and peripheral pulse oximetry

5) Improvement in selected laboratory parameters: blood haemoglobin, differential and total leukocyte counts, liver enzymes, renal functions, acute phase reactants, serum IL-6 and other selected cytokines, serum muscle enzymes (CK, CPK), serum ferritin, serum d-Dimer, anti-oxidant markers, serum BNP (cardiac function)

6) Serological Protective Antibody Assay (IgM and IgG)

7) Radiological Improvement on digital chest Xray and HRCT chest

8) Drug related: side effects and toxicity, and tolerability

9) Health status: WHO QOL (Appendix M) brief, health related behaviour habit and fitness questionnaire based on visual analogue scale (See Appendix N)

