There is no universally accepted system to classify or stage the disease into various categories like mild, moderate or severe at onset of symptoms or during the early part of the disease. A large proportion of patients remain asymptomatic or with mild symptoms and recover completely as described above. It is also easier to comprehend the severe stage characterized by progressive respiratory failure or ARDS invariably necessitates need for supplemental oxygen or a ventilation assist device. Pneumonia is often an early occurrence along with fever, cough and breathlessness in the large majority and patients are expected to recover without any severe progression of respiratory status or any other complication. So the presence of pneumonia does not necessarily mean severe COVID-19. It may be more suitable to label COVID-19 severe if there is a low arterial oxygen saturation (as evident by pulse oxymetry) and a requirement of oxygen and or ventilation device and some of these patients will progress to a life threatening situation which needs critical ICU support in an ‘emergency situation’. Objective measures of respiration and cardiovascular system can define the severity of the disease in the few patients who rapidly worsen. As mentioned above (See Table 3), there are several other complications which are life threatening and can turn the balance towards a severe or an emergency status; most important being septicemia and septicemic shock. It must be remembered that patients with mild disease at onset can infrequently rapidly progress to severe disease and that some patients may die within few days of onset of illness.

An expert group has described 4 stages as follows; Mild (without any risk factors/ comorbidities and managed as outpatient), Moderate (dyspnoea, hypoeximia, and infiltrates/ consolidation on chest on X-Ray/ CT scan, and needs to be hospitalized for treatment), Severe (severe respiratory illness , respiratory rate > 30/min, SPo2- <93%, PaO2/FiO2 <300, and lung infiltrates >50% within 24- 48 hours and requiring ICU care ), Critically Ill (ICU care , respiratory failure and/or ARDS with need of mechanical ventilation, Septic shock and Multiple organ dysfunction syndrome and cytokine storm syndrome). (International Pulmonologist’s Consensus On Covid-19.Available at [https://www.unah.edu.hn/ dmsdocument/](https://www.unah.edu.hn/%20dmsdocument/)9674-consenso-internacional-de-neumologos-sobre-covid-19-version-ingle. Accessed at 03 May 2020).

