# CONSENT, SELECTION, SCREENING, and ENROLLMENT

Study patients will be served on first come first serve basis as per the protocol.

Consenting and eligible patients will be enrolled as soon as possible in a COCID-19 management facility and the study intervention begun. It is important that symptomatic patients suspected for COVID-19 on clinical grounds are quickly evaluated for eligibility. It is important to enroll the patient as close to the onset of symptoms as possible. As described above, this study is dealing with patients of COVID who are ‘non-emergent’ which means mild and moderate disease (pneumonia) which does not require emergency or critical care (see section on inclusion and exclusion criteria).

An ‘Patient Information Sheet’ (Appendix F) in the language understood by the patient will be provided to each patient for study and discussion prior to enrollment. The information fact sheet will describe the overall design of the study and the rationale, benefit and side effect profile of the study drug interventions, and other aspects of the study.

Patients will be selected from the outpatient or inpatient facility in COVID-19 medical centres/ hospitals. The study will be explained to the volunteer patients and those willing to sign the informed consent (Appendix G) will be screened for eligibility as per the inclusion and exclusion criteria in the protocol.

Though it will be preferable to enrol patients with diagnosis confirmed by a positive RT-PCR assay using a nasal or throat swab in a standardized procedure, a patient with a clinical diagnosis of COVID- 19 as described below will be eligible.

Eligible patients will be enrolled using a simple randomization table (provided to the investigator) in a block of 20 patients each to either of the two study arms - SOC plus Ayurveda drug or SOC. As the target sample size is 70 patients in each arm, the first block of randomized allocation will be of 10. The study randomization will be carried out by the investigator.

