# 10. PATIENT POPULATION

The patients will be largely drawn from COVID-19 clinics and outpatients in various medical colleges and hospitals. All patients will be admitted in the hospital for standard care and those willing to participate in the study will be screened and enrolled as described above. Only patients with mild to moderately severe symptoms will be selected as described above. If the patients progress to a severe stage of illness as described below, they will be withdrawn from the study but the investigator will be encouraged to follow the patient ill study completion at week 12 and during this period record the hospital management, course of illness , final outcome and post recovery health status as described in this protocol.

- 1. Inclusion Criteria:

1. Typical Clinical presentation of acute onset febrile illness with cough and a RT_PCR based laboratory confirmation test for COVID-19
2. Patients with either sex, 21to 69years age
3. Patients with Mild to Moderate COVID-19 as described below
4. All patients must agree not to share medication
5. Patients willing to participate and sign an informed consent
   Note: The criteria for mild to moderate COVID-19 are based on the WHO recommendations (See Section 2.5 above with WHO Table on clinical syndromes of COVID-19 and include Mild disease and Uncomplicated Pneumonia but not severe disease which requires any form of intensive care such as invasive techniques for supplemental oxygen or ventilation and life support systems, and absence of any life threatening complications (such as severe respiratory failure, adult respiratory distress syndrome, septicaemia shock and other complications shown in Table 3 above)
   1. Exclusion Criteria

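### Pneumonia is both an eligible entry category and a secondary outcome event with no at-risk set defined, so the between-arm comparison mixes baseline status with new events

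*Combined protocol and SAP*

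**What the plan says.** **Entry.** Section 3 (Rationale) states: "The mild to moderate cases of COVID-19 will belong to the categories of ‘Mild’ and ‘Pneumonia’ as described by WHO". The note to the inclusion criteria in Section 10 says the eligible categories "include Mild disease and Uncomplicated Pneumonia but not severe disease". The section on consent, selection, screening and enrolment describes the target group as "mild and moderate disease (pneumonia) which does not require emergency or critical care".

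**Outcome.** Section 11.2, item 2, lists "onset of clinical pneumonia, pneumonia diagnosed on chest X-Ray or CT scan, time to supplemental oxygen" among its events, and its clock is given as "Timelines (days counted from onset of illness". The primary outcome in Section 11.1 runs from the day of randomisation. Item 3 takes the "Proportion OF patients developing an event that reflects clinical or otherwise improvement of worsening", using much the same list of events. The synopsis repeats both items.

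**Analysis.** Section 17.2 says that secondary measures will be compared between the two arms with a Bonferroni correction. Nothing there, or in the enrolment section, restricts the pneumonia outcomes to patients without pneumonia at entry, adjusts for baseline pneumonia, or stratifies randomisation by it.

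**Data available.** Section 15.1 and Appendix A schedule a chest X-ray and HRCT at baseline. The daily progress report (Appendix J) has a pneumonia row from D1 and does not separate new from pre-existing disease.

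**The concern.** An outcome meant to show whether the drug prevents progression should count events that the drug could have prevented. Pneumonia already present at randomisation is not such an event. With the clock set at onset of illness, it still receives a valid event time and, absent a rule to the contrary, enters the comparison.

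Two things follow. A real reduction in new pneumonia is diluted by a block of events common to both arms. And because randomisation is not stratified by baseline pneumonia, a chance imbalance at entry can show up as a difference in outcome. Two analysts could also read the items differently and report different results from the same data.

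**Working it through.** The plan has no figure to reproduce. Section 17.1 calls 70 per arm a convenience size without a power calculation, and no pneumonia rate is stated for entry or follow-up. The rates below are assumptions, shown over a range.

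**Notation.** q is the share with pneumonia at entry; r is the rate of new pneumonia among those free of it.

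**Step 1: what would be reported.** Reported proportion = q + (1 − q) × r. Take r = 0.20 (control) and 0.10 (drug), a true risk ratio of 0.50. At q = 0.30, control is 0.30 + 0.70 × 0.20 = 0.44 and drug is 0.30 + 0.70 × 0.10 = 0.37.

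| q | Control v drug | Difference (points) | Risk ratio | Baseline cases among control-arm events |
|---|---|---|---|---|
| 0 | 20% v 10% | 10 | 0.50 | 0% |
| 0.10 | 28% v 19% | 9 | 0.68 | 0.10/0.28 = 36% |
| 0.30 | 44% v 37% | 7 | 0.84 | 0.30/0.44 = 68% |
| 0.50 | 60% v 55% | 5 | 0.92 | 0.50/0.60 = 83% |

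**Step 2: when baseline cases are the majority.** Their share of counted events is q / (q + (1 − q)r). This exceeds one half when q > r/(1 + r). For r = 0.10, 0.20, 0.30 and 0.40 the threshold is 9%, 17%, 23% and 29%.

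**Step 3: chance imbalance at entry.** The standard error of the arm difference in baseline pneumonia is √(2q(1 − q)/70): 7.7 points at q = 0.30 and 8.5 points at q = 0.50. A fraction (1 − r) of any imbalance, here 80% to 90%, carries into the reported difference. That is about 6 to 8 points per standard error, against a diluted effect of 7 or 5 points.

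**Step 4: power.** Two-proportion z-test, two-sided 0.05. All randomised patients give 70 per arm; the at-risk set gives 70(1 − q) per arm.

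| New pneumonia | q | All patients | At-risk set (n per arm) |
|---|---|---|---|
| 20% v 10% | 0.30 | 13% | 28% (49) |
| 20% v 10% | 0.50 | 9% | 21% (35) |
| 30% v 15% | 0.30 | 24% | 43% (49) |
| 30% v 15% | 0.50 | 15% | 32% (35) |

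With nobody entering with pneumonia, the two scenarios have 38% and 57% power. All these figures ignore the Bonferroni correction and the 15–20% withdrawal assumed in Section 17.1, so they are optimistic.

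**The case against.** **The wording may already mean new events.** Onset and developing can be read that way, and baseline imaging would make that reading workable. This stands in part: no sentence says that baseline pneumonia counts. But the illness-onset clock points the other way and nothing settles the matter.

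**The entry share is unknown and may be low.** The enrolment section asks for patients as close to symptom onset as possible. Against that, the discussion of classification and staging in Section 2 says "Pneumonia is often an early occurrence along with fever, cough and breathlessness in the large majority", and the imaging paragraph reports abnormal CT in half of an asymptomatic cohort. Neither gives a rate for this trial. A reader might take the 91% pneumonia figure in Table 3 as the entry share. It is a complication rate in a retrospective hospital series and can include pneumonia arising later, so it does not serve.

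**The timelines also have a descriptive purpose.** Describing the course of illness and the timing of complications is a secondary objective (synopsis, item c; Section 4). Pneumonia before enrolment belongs in that description. This stands, and the concern is limited to the between-arm comparison.

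**Randomisation balances baseline pneumonia in expectation.** It does. The comparison is diluted and noisier, not systematically biased.

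**Oxygen is less clear than pneumonia.** A reader might infer that patients on oxygen are plainly eligible, since Section 3 says: "Mere need for supplement oxygen using non-invasive means will not negate the classification of mild to moderate COVID-19". But the Section 10 exclusion guidance lists oxygen support for over one hour, and the WHO pneumonia category as described in Section 2 has no need for supplemental oxygen. These passages conflict. Nothing supports extending the point to steroid use at entry.

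**Item 3 need not be one composite.** A reader might see a single proportion that adds improvement to worsening. The text does not say so; a proportion for each listed event is the ordinary reading.

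**Conclusion.** The point holds as a defect in how two secondary outcomes are defined for the arm comparison. Pneumonia is an entry category and an outcome event, the clock starts before randomisation, and no at-risk set is given.

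Its size depends on the unstated entry share. Under the assumed halving from 20% to 10%, an entry share of 30% to 50% moves the risk ratio from 0.50 to 0.84–0.92. A reader might conclude that these outcomes mostly measure baseline status. That would be true once the entry share passes roughly 9% to 29% (new-event rates of 10% to 40%), but the documents do not show where this trial falls.

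The primary outcome is unaffected and the trial is declared exploratory, so this is a correction worth making, not a threat to the main result.

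**What to change.** For the between-arm comparison in Section 11.2, items 2 and 3:

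- Count clinical and imaging pneumonia only when it first occurs after randomisation, in patients without it on baseline examination, X-ray and HRCT.
- Measure time from randomisation. Moving the origin alone is not enough, because patients with existing pneumonia would then have an event at Day 0.
- Report patients with baseline pneumonia under item 7, as radiological improvement or worsening.
- Apply the same new-event rule to supplemental oxygen for any patient on it at baseline. Reconcile Section 3, the WHO description in Section 2 and the Section 10 exclusion guidance on whether such patients are eligible.

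Keep the illness-onset timelines for the descriptive objective. Settle the wording before outcome data are seen.

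The cost is wording in the protocol and analysis plan; baseline imaging is already scheduled. The denominator shrinks (49 or 35 per arm at entry shares of 30% or 50%). Power rises on the assumed rates but stays low, so results should be presented as estimates with confidence intervals.
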